# STUDY SUMMARY

| Study Title | A tailored intervention to reduce sitting behaviour in people with Type 2 Diabetes: A randomised-controlled feasibility study |
| --- | --- |
| Short title | REgulate your Sitting Time (RESIT) |
| Study Design | Randomised controlled feasibility trial |
| Study Participants | Adults with Type 2 diabetes |
| Planned Size of Sample | 70 participants |
| Planned Study Period | 18 months |

# ROLE OF STUDY SPONSOR AND FUNDER

The Sponsor of this study is the Brunel University London. The sponsor is responsible for the overall conduct and management of the study. The funder, Diabetes UK, has reviewed the study protocol as part of the grant award process. The funder will not have any involvement with the conduct of the study, data analysis or presentation of the findings.

# ROLES AND RESPONSIBILITIES OF STUDY MANAGEMENT COMMITEES

INVESTIGATOR COMMITTEE

All investigators for the project will meet every 3 months to discuss progress of the study, strategy for delivery, risk management, review of safety and efficacy data, and dissemination of findings.

TRIAL COORDINATION COMMITTEE

The trial coordination committee will comprise of the Chief Investigator, Research Assistant and Trial Coordinator and will meet fortnightly to discuss day-to-day running of the project. Updates from these meetings will be provided for the investigator committee and PSC.

PROJECT STEERING COMMITTEE (PSC)

The PSC comprises of an independent Chair, an independent expert in the study area, a lay person, the principal investigator and one co-investigator and will meet every 6 months. The PSC will advise, via the Chair, on relevant aspects of the project to the funder, sponsor and host institution. It will monitor progress of the project, protocol adherence, substantial protocol amendments and participant safety. The PSC will also advise the investigators on all aspects of the project.

PATIENT AND PUBLIC ADVISORY GROUP (PPAG)

The PPAG will implement their terms of reference from the onset which will focus on three core areas; supporting the development and direction of the research, development of information resources and dissemination of research findings. The PPAG will be comprised of the immediate project group, an independent chair, a CCG diabetes lead for the local area, a diabetes nurse and two patients with Type 2 diabetes (T2D). The PPAG will meet every 3 months and have input as below:

MANAGEMENT OF THE RESEARCH: Advisory members will help to ensure the recruitment process is practical, feasible and effective. Members will provide ideas on recruitment methods, how to encourage people with T2D to volunteer, and how to raise the subject of sitting behaviour with the target population. Members will feedback on the protocols planned for delivery within the study and will help to solve issues that may arise during delivery of the study.

DEVELOPMENT OF INFORMATION RESOURCES: Advisory members will help to make language and content of information resources appropriate and accessible to potential volunteers, including questionnaires, information leaflets and consent forms. This will aid recruitment and help potential volunteers to make informed choices about their participation.

DISSEMINATION TO THE DIABETES COMMUNITY: Advisory members will help interpret the reporting of the research and provide feedback on outputs to ensure disseminated outcomes are important to people with T2D. Members will assist with interpreting the research findings in the context of identifying themes that the researchers might miss, help check the validity of the conclusions from a diabetes patient perspective, and highlight findings that are more relevant to people with diabetes. They will also help in planning of a public outreach event to share the findings with the diabetes community and health professionals in the area.

# PARTICIPANT FLOW DIAGRAM

[figure not shown]

# STUDY PROTOCOL

## BACKGROUND

There are more than 3 million people with Type 2 diabetes (T2D) in the UK, costing the NHS 10% of its annual budget (1). People with T2D have a high risk of cardiovascular disease (CVD), early death, poor psychological wellbeing and a burden of diabetes-related complications such as neuropathy, nephropathy and retinopathy that reduce quality of life (2-4). Improving glycaemic control is important for reducing the onset of these secondary outcomes (5, 6) and effective interventions thus need to be identified.

People with T2D spend 8.0-9.5 hours/day sitting (7-9). Sitting (sedentary behaviour) has been detrimentally associated with CVD (10); a leading cause of death in T2D (1). Each hour of sedentary time is detrimentally associated with CVD risk markers in people with T2D including waist circumference, insulin resistance and high-density lipoprotein cholesterol (HDL) (7). Importantly, the detrimental associations of sedentary time with T2D, CVD and psychological wellbeing are independent of time spent in moderate-to-vigorous physical activity (MVPA) (10, 11). At least 60-120 minutes/day of MVPA may be needed to protect against the increased mortality risk associated with high amounts of sitting (12, 13), which is an unrealistic target for most people. In T2D, each 1 minute increase in sedentary time is related with a 0.12 minute increase in time spent in hyperglycaemia (7.4 minute increase in hyperglycaemia for each extra hour of sitting) (14). Hyperglycaemia increases CVD risk (1) and is associated with poor psychological wellbeing (15). Each hour of sedentary time is also unfavourably associated with waist circumference, insulin and a clustered CVD risk score, while each break in sedentary time is associated with lower waist circumference and improved HDL (7, 8). Reducing total and prolonged sitting is thus an important target to reduce CVD risk and poor psychological wellbeing in people with T2D.

Experimental evidence demonstrates that breaking up sitting time with 2 minute bouts of light-intensity walking every 20 minutes improves postprandial (post-meal) glucose over 5 hours in healthy adults (16-18); 5 minutes of standing or light walking every 30 minutes improved postprandial glucose and insulin in people at high risk of T2D over 7.5 hours and persisted into the following day (19); and 20 minutes of light walking every hour over 6.5 hours improved postprandial glucose, triglycerides and resting blood pressure in inactive adults (20). Breaking up sitting with light walking or light body weight resistance exercises for 3 minutes every 30 minutes acutely improved postprandial and nocturnal glucose, insulin, triglycerides and blood pressure in people with T2D (21-23). The magnitude of response in these studies is greatest in individuals with poor metabolic health, such as T2D. People with T2D should thus target reductions in sitting in addition to increases in MVPA to optimise management of their disease, which is recommended by the American Diabetes Association (24). The importance of reducing sitting time in this group is emphasised by observations that only 4-6% of UK adults meet the recommended 150 minutes/week of MVPA when measured using accelerometry (25). Interventions to reduce sitting may therefore be more achievable and better tolerated in people with T2D (26). However, there is a paucity of studies that have evaluated interventions for reducing sitting in people with T2D and strategies to achieve this in healthcare do not exist. This will be addressed by this project through the evaluation of a novel evidence-based patient-tailored self-regulation intervention based upon effective behaviour change techniques (BCTs) for reducing and breaking up sitting (27).

A number of interventions using various BCTs and self-monitoring tools have effectively reduced sitting in the general population and office workers. For example, a workplace intervention targeting reductions in sitting using a wrist-worn prompt device coupled with goal setting reduced sitting by 25 minutes/work shift over 3 days and reduced prolonged sitting (28). The use of a paper-based sitting diary as part of multicomponent workplace interventions (including providing information, goal setting, health coaching, and height-adjustable workstations) led to 50-125 minute/day reductions in workplace sitting after 4-12 weeks and 45-83 minute/day reductions after 12 months (29-31). Using computer prompt software and phone apps as part of an 8-week multicomponent workplace intervention (including providing information, goal setting and health coaching) reduced prolonged sitting by 39 minutes and increased the number of breaks from sitting by 7.8 per work shift (32). A phone app for self-monitoring sitting in addition to goal-setting and individualised feedback reduced daily sitting by 40 minutes and increased breaks from sitting by 5.7 per day after 1 week in healthy adults (33). In overweight/obese adults, after an education session on sedentary behaviour, use of a self-regulatory phone app that prompted participants to break up their sitting and provided feedback on sitting led to a 44-47 minute reduction in daily sitting after 1 week (34). Interventions incorporating BCTs such as providing information on health consequences, problem solving, goal setting, action planning, social support, restructuring the physical environment, prompts and cues, and self-monitoring thus appear to have promise for reducing sitting. However, there is a lack of literature evaluating the efficacy of reducing sitting in people with T2D. In participants with T2D, self-monitoring using a pedometer as part of a cognitive-behavioural intervention led to an increase in steps per day after 3 months and 1 year (35); while sedentary time reduced at 3 months but returned to baseline levels after 1 year; likely because the intervention did not specifically target changes in sedentary time. The lack of tested interventions in T2D will be addressed by this project.

With regards to the most promising BCTs used in previous interventions for reducing sitting, a systematic review of 38 interventions (with varying methodologies) in the general population identified that self-monitoring and problem solving were the most promising BCTs for reducing sitting, alongside restructuring the social and physical environment (27). While retrospective systematic reviews can help to identify the BCTs used in a combination of past effective versus ineffective interventions, what is needed are trials that are tailored to the needs of the population, using BCTs within one intervention that have been found to be included in effective trials, like those mentioned above. Furthermore, tailored behaviour change strategies are more likely to lead to effective outcomes, as seen when delivering interventions using Motivational Interviewing (36, 37) and those based on Self-Determination Theory (38). Thus, enabling participants to select their own tools (e.g. sitting diary, wearable tracker, phone app or computer app), while ensuring that the same BCT strategy is being used (e.g. self-monitoring of behaviour), may be a more effective approach to reducing sitting as one-size does not fit all. Although the findings of the relatively short interventions discussed above that included self-monitoring of sitting are promising, participants in these studies were not provided a choice of which self-monitoring tools they could use. One previous intervention comprised of reviewing sitting time, providing feedback on sitting and allowing participants to choose six different goals to reduce sitting, led to a 96 minute/day decrease in sitting after six weeks in older adults (39). This study shows promise but there is no research that has evaluated the effectiveness of people with T2D selecting their own tools to reduce sitting.

This study will test the more promising BCTs for reducing sitting in adults identified in previous systematic reviews (27, 40) alongside others found in effective interventions mentioned above, in a controlled tailored intervention. The intervention will allow autonomy via provision of participant-led choices of the “*delivery”* of the BCTs (e.g. via a phone app, computer app, wearable tracker and/or paper diary). However, as an intervention package, all participants will have access to the same BCTs. This is in line with a core NICE recommendation for the use of tailored care in the management of T2D (41) and the Diabetes UK research strategy target for improving self-management of diabetes.

## RESEARCH OBJECTIVES

The main objectives of this feasibility study are to:

1. Establish and refine a recruitment strategy for people with Type 2 diabetes.
2. Determine participant attrition in the trial.
3. Determine completion rates for outcome measures (and whether these are sufficiently high to provide accurate data in a full trial).
4. Assess the acceptability of randomisation to the intervention and usual care.
5. Assess the acceptability of the intervention and data collection to participants.
6. Assess intervention fidelity and adherence.
7. Explore the feasibility of collecting data (as below) to inform the design of the health economics component in a full RCT.

The secondary objectives are to derive preliminary estimates of the effect of the intervention on participants’:

1. Device measured daily sitting time, prolonged sitting time, breaks from sitting and light and moderate-to-vigorous physical activity.
2. Cardiometabolic risk markers (BMI, waist circumference, body fat%, fasting glucose, glycated haemoglobin, lipids, blood pressure)
3. Fatigue, self-efficacy for reducing sitting time, psychological wellbeing, mood, physical functioning, musculoskeletal symptoms and quality of life.

## STUDY DESIGN/METHODS

### Study design

This will be a mixed methods randomised controlled feasibility trial conducted and reported in accordance with CONSORT guidelines (42) and the TIDieR checklist (43). After baseline measures, participants will be individually randomised to one of two conditions (intervention and passive control). The 24-week intervention period will then commence and follow-up measurements will be repeated at 12 and 24 weeks after baseline measures.

This trial is likely to be conducted before society has returned to ‘normal’ after the COVID-19 pandemic. As such, contingency plans with regards to intervention delivery and data collection methods during pandemic restrictions are detailed below.

### Participants

Participants will be aged 18-85 years with physician diagnosed or self-reported T2D who are able to ambulate unassisted and self-report sitting for ≥7 h/day (this is the threshold above which mortality risk increases) (44, 45). Exclusion criteria will be using insulin medication, unable to communicate in English, pregnant, and cognitive or physical conditions interfering with the ability to stand and ambulate (with or without the use of a walking aid). Diagnosis of T2D will be confirmed from the fasting glucose measure taken at baseline. Individuals with readings below the diabetes range (7 mmol/L) will at this stage be excluded from the study.

**COVID-19 contingency:** If it is not possible to take glucose measures at baseline due to COVID-19 restrictions, participants will not be required to fast overnight prior to data collection. Participants in this case will need to self-report Type 2 diabetes diagnosis. Each participant’s GP will be notified of their participation in the study; GPs will be asked to inform the research team if their patient does not have a Type 2 diabetes diagnosis.

### Sample size

Sample sizes between 24 and 50 have been recommended for feasibility studies (46, 47). A sample size of 70 will be used in this study (n=35 in each the intervention and control groups) to allow for the different combination of intervention tools that the participants are able to select from and to allow for drop out.

### Recruitment

Participant recruitment will be via GPs where study information will be sent out via postage using Docmail and via the GP Practice SMS text messaging service (see Docmail GP invitation letter and SMS content in additional files) to potentially eligible patients using a database search. The GP invitation letter will also be provided during consultations if the GP or nurse considers their patient to be potentially eligible. All NHS recruitment is being supported by the London North West local Clinical Research Network. This is in addition to recruiting via local Diabetes UK support groups (via email send out of the Participant Information Sheet and attendance at group sessions) and social media (including a video professionally developed by Health & Care Innovations; the script for this is based on information from the PIS). A link to the video will also be accessible from the project webpage ([tinyurl.com/RESIT-information](https://tinyurl.com/RESIT-information)), which is another route that potentially eligible participants may find information about the study. Participants recruited via these latter routes will be mapped back to their GP Practice. Potentially eligible participants will be asked to express their interest by email, returning a reply slip to the research team, or by scanning a QR code provided on recruitment materials to pass their name and email address (via Qualtrics) to the research team. A researcher will then contact interested volunteers by email/telephone to screen them. Individuals who remain potentially eligible will then be invited to complete baseline data collection after providing informed consent.

### Randomisation

Eligible participants will be randomised by an independent researcher in a 1:1 (intervention:control) ratio using a fixed block size of 4. Block randomisation is used to increase the likelihood of achieving balance of numbers in the allocation to groups given the relatively small sample size, i.e. each aim is more likely to contain an equal number of individuals.

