These tools will be provided to participants (face-to-face or via post) or downloaded onto their phone/computer under guidance from the research assistant following completion of the online programme. Participants will be permitted to choose a maximum of one tool from each of these categories (e.g. one smartphone app, one computer prompt, one wearable device or paper-based tracker) but they are not required to choose a tool from every category. For example, a participant may choose a smartphone app and a wearable device only. The choice is theirs, thus making the intervention person-focused to increase potential effectiveness. This is consistent with Self-Determination Theory and accepted ways of boosting intrinsic motivation. The research assistant will provide a guidance document to the participant for each tool selected that will explain how to download and how it works. Participants will not receive any instructions on how often they should engage with the tools that they select given that the intervention is person-focused. The self-selected behaviour change tools used can be changed during the intervention period if a participant reports to the health coach or research team that they are not engaging with the tool. This might be due to reasons such as technical complexity, impracticality or a dislike of the tool. If there are any problems with using any of the tools during the intervention, participants will be able to contact the research assistant for troubleshooting.

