### Control group

Participants randomised to this group will receive usual care. They will complete the same measurements as the intervention group. After the trial has concluded, they will be offered use of the psychoeducation programme and the self-selected behaviour change tools.

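### A fixed, disclosed block size of 4, with allocations visible to study staff, could let an informed team know up to about a third of the 70 allocations in advance

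*Protocol*

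**What the plan says.** The Randomisation section of the protocol states that eligible participants will be "randomised by an independent researcher in a 1:1 (intervention:control) ratio", "using a fixed block size of 4". It names no stratification factor and no varying block size. Its stated reason is balance: "Block randomisation is used to increase the likelihood of achieving balance of numbers in the allocation to groups". The Study design section places randomisation after baseline: "After baseline measures, participants will be individually randomised to one of two conditions (intervention and passive control". The Sample size section plans 70 participants, "n=35 in each the intervention and control groups".

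Other sections bear on who can see allocations:

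- **Control group:** "Participants randomised to this group will receive usual care". The intervention arm receives an online programme, health coaching and self-selected tools. Staff blinding is not described.
- **Self-selected behaviour change tools:** intervention participants get their tools in person or by post, or have them "downloaded onto their phone/computer under guidance from the research assistant".
- **Physical function, COVID-19 contingency:** the remote tests are done on a video call with the research assistant. Under Data collection, these tests are among the measures taken at baseline.
- **Recruitment:** a researcher contacts and screens volunteers, and those still potentially eligible are then invited to baseline.
- **Roles and responsibilities:** the Chief Investigator, Research Assistant and Trial Coordinator meet every two weeks on day-to-day running.

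**The concern.** Blocked allocation stays concealed only while staff cannot work out where they are in a block. A fixed block of 4, written into a document the study team works from, reveals the block boundaries to anyone who keeps count. The fourth allocation in each block is then always determined, and the third is determined whenever the first two match.

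Having an independent researcher hold the list does not prevent this, because the deduction uses past allocations and not the list. Here past allocations are visible. One named role, the research assistant, learns who is in the intervention arm by setting up tools. Under the COVID-19 contingency, the same role also deals with people who have not yet been randomised.

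Foreknowledge would leave room to encourage one volunteer more than another, or to bring forward or delay a baseline session so that a person falls at a known place in the sequence. Deriving preliminary effect estimates is a stated secondary objective (Research objectives), and at about 35 per arm a few steered entries could shift a mean.

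**Working it through.** **Inputs.** Block size 4, fixed, and ratio 1:1, so 2 intervention (I) and 2 control (C) per block (Randomisation). Total 70 (Sample size). Assumed: one unstratified list, and an observer who knows all earlier allocations in order.

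**The plan's own figure.** 70 / 2 = 35 per arm, as stated. The total rests on a recommended range for feasibility studies plus an allowance, so there is no power formula to reproduce.

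**Allocations known with certainty.** An allocation is forced once one arm's two places in the block are filled. There are 6 equally likely sequences:

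- IICC and CCII: the third and fourth are forced (2 each).
- ICIC, ICCI, CICI, CIIC: only the fourth is forced (1 each).

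Expected forced per block = (2 × 2 + 4 × 1) / 6 = 8/6 = 4/3, or one third of the block.

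70 = 17 × 4 + 2. The first two places of the unfinished block are never forced, so the expected total is 17 × 4/3 = 22.7, and 22.7 / 70 = 32.4%.

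**Success of guessing the under-filled arm.** Chance of a correct guess by place in the block:

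- First: 1/2 (arms level).
- Second: 2/3 (two of the three remaining places belong to the arm that is behind).
- Third: (1/3 × 1) + (2/3 × 1/2) = 2/3.
- Fourth: 1.

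Sum = 2.833 of 4. Over 70: (17 × 2.833 + 0.5 + 0.667) / 70 = 49.33 / 70 = 70.5%, against 50% with no information.

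**Alternatives.** Fixed sizes are by the same enumeration. The varying sizes are by simulation (4,000 runs of 70, sizes equally likely, the observer knowing the set of sizes but not the order).

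| Block scheme | Share of 70 known with certainty |
|---|---|
| Fixed 4 | 32.4% |
| Fixed 6 | 23.7% |
| Fixed 8 | 18.5% |
| Random 4 and 6 | about 5.5% |
| Random 2, 4 and 6 | about 4.0% |

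The gain is in certainty. Guessing the arm that is behind needs no knowledge of block size, because the arms are level at the end of every block. Its success is 70.5% with fixed 4 and 67.9% with fixed 6, so a 4-and-6 mix lies between those values, at about 69%.

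**Balance at 70.** With fixed 4, the 17 full blocks give 34:34. The last two places differ with probability 2/3, giving 35:35. Otherwise (1/3) the split is 36:34 one way or the other. With random 4 and 6, all sizes are even, so 70 falls at the end of a block or after 2 or 4 places of an unfinished one. After 2 places the difference is 0 or 2. After 4 places of a block of 6 it is at most 3 − 1 = 2. The maximum is therefore 2 under either scheme.

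**The case against.** The strongest objection is that the protocol does not show anyone holding the required knowledge. It does not say that the person who screens is the research assistant, that the fortnightly meetings discuss allocations, or who takes consent, and it never describes the trial as open-label. The observer would also need the order of randomisation. Participant numbers are issued in order of consent (Confidentiality and record keeping), which helps to reconstruct it but may not match it. All of this stands, and it makes the figures conditional maxima.

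It is also fair that room to act is limited. Volunteers come forward themselves after invitation, entry rests largely on set criteria, and randomisation follows consent and baseline measures. If randomisation waits for the baseline activity monitor, worn for up to 8 days, several people may be in process at once and a recruiter may not know a volunteer's place in the block. That narrows the opportunity but does not close it, since encouragement and the timing of sessions remain discretionary.

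Finally, the preliminary effects are to be summarised descriptively, and the calculation measures predictability, not bias. That is correct, and it limits the point to a cheap improvement.

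A reader might also infer that the 35 per arm in the Sample size section contradicts blocks of 4, because 70 is not a multiple of 4. The documents do not support this. The Randomisation section claims only a greater likelihood of balance, 35 is the planned size under 1:1 allocation, and 36:34 is harmless in a feasibility trial.

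**Conclusion.** The point holds as a weakness in a design choice. It is neither a contradiction nor a wrong figure. Fixing and disclosing a block size of 4 leaves up to 22.7 of 70 allocations (32.4%) certain in advance, and up to about 70% guessable, for a team that knows all earlier allocations in order on one unstratified list. That staff can see allocations is a sound inference from the nature of the two arms and the lack of any described staff blinding. That the same people recruit and know the full order is plausible but not stated.

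A reader might go further and conclude that recruiters will know a third of allocations, or that the results on acceptability of randomisation will be distorted. The documents do not support either. The first turns a condition into a fact, and for the second no mechanism is apparent. What can be said is that an avoidable opportunity for selection exists, which could bias the preliminary between-arm estimates by an amount that cannot be calculated from the protocol.

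**What to change.** Replace the fixed block of 4 with randomly permuted blocks whose size varies at random, for example 4 and 6. Take the block sizes out of the protocol and keep them in a restricted document held by the independent researcher. The protocol need say only that blocks of varying, undisclosed size are used. Certain foreknowledge then falls from 32.4% to roughly 5-6%, even for someone who knows the set of sizes. Guessing the arm that is behind would still beat chance, as under any blocked scheme.

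The cost is a list generated differently before the first randomisation and a short edit to the Randomisation section. Balance does not suffer at the planned total: the arm difference at 70 is still at most 2.
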